### The national school feeding programme in Mali

In line with the National Decentralisation Policy and the 2009 National School Feeding Policy, programme implementation is decentralised to the community level, involving the communes and School Management Committees (CGS). The central government allocated nearly 5 million USD (2.6 billion CFA) in 2010 and 5.8 million USD in 2011 (3.1 billion CFA) from the national budget for food, cooking equipment and infrastructure rehabilitation and construction [8]. Funds are channelled directly through the Ministry of Finance to its Regional Offices which in turn send funds to the communes. Food commodities are procured from local markets by the communes or by the CGS. To date, there is no fixed food basket nor fixed ration specification. The budget allocated for food procurement is based on student enrolment figures obtained by the Ministry of Education and price estimates for staples at the beginning of the school year. The budget covers staples, including cereals and pulses and oil. Fresh vegetables to complement the school feeding ration are contributed by parents and the community through cash or in-kind contributions. Cooks are generally organised on a voluntary basis (also considered as the contribution to the program from the community) through the CGS.

Food provision consists of a school lunch meal served at noon (school is from 8 am to 12 am and then again from 3 pm to 5 pm). The food mainly consists of staples (rice, millet or sorghum) enriched with condiments, vegetables, vitamins and minerals depending on the source of provision. Figure 1 captures the key activities in the food procurement process currently in use in the national programme. Enrolment figures are collected by the Centres d’ Animation Pedagogicue (CAP), the equivalent of district education offices, through the CGS and passed on to the mayors to estimate the food requirements for school feeding. Mayors receive budgets from the Ministry of Finance on the basis of the enrolment/food requirements, then issue tenders, on the basis of a credit advance, to certified service providers (traders) to procure the food. The service providers (traders) then purchase the food from the market or from small-holders, and deliver it to the relevant schools.

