**Figure 5 F5:**
[figure not shown]
Potential impact of HGSF on commune food demand.

The size of the shift depends on the extent of the substitution effects and on the size of the market considered. Substitution occurs when households reduce the domestic consumption of food because children are fed in school. At one extreme, there is full substitution: families do not provide any additional food to children fed in school or any other household member in excess of the school food ration. Food provided in school entirely substitutes for food normally consumed in the home. The result is an increase in household savings and consumption of non-food items. In this case, there is no shift of the demand function (D_0_) and HGSF does not have price or output effects. There is still a distributional effect of the intervention if food is purchased from small-holders rather than large farmers. Profits of large farmers will in this case decrease whilst profits of smallholder farmers increase. Full substitution, however, is unlikely to occur. The largest substitution is likely to occur when households interpret the school food ration as a cash transfer. In this, theoretical, case the income equivalent of the ration is spent following income elasticities. Considering that the areas of intervention are very poor, assuming an income elasticity of food of 0.6 to 0.8 and a food share of 0.8, we understand that only about half of the HGSF transfer would eventually be spent on food and the food demand function shifts to D^*^. However, studies show that rarely do people interpret food transfers as cash transfers and that people tend to attach some preference to the food received and thus consuming food beyond what the income elasticities would suggest. Therefore, the final shift in the demand curve is likely to happen somewhere between the curves D^*^ and D_1_.

The size of the demand shift also depends on the size of the market considered. If we are considering the national rice market, the shift is extremely small and the price and output effects are likely to be negligible [10]. The effect is larger at the commune level if food is procured locally. However, some of the food may be purchased outside the commune and, therefore, the shift of the demand function at the commune level would be smaller than the one depicted in Figure 5.

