**Figure 11 F11:**
[figure not shown]
**Programme theory of impact on nutrition.** The nutritional impact is mediated by the extent of food substitution effects within the household, and the use of the energy intake by the child and her siblings. The reduction in malnutrition via diet diversification and the absorption of micronutrients in the body can have direct effects on cognition. Better nourished children may learn better while in class and outside class.

a) The nutritional impact is mediated by the extent of food substitution effects within the household, and the use of the energy intake by the child and her siblings.

b) The reduction in malnutrition via diet diversification and the absorption of micronutrients in the body can have direct effects on cognition.

c) Better nourished children may be best positioned to learn while in class and outside class.

These three issues will now be discussed:

a. Substitution effects

Building on [17,18], we provide a simplified programme theory of the nutritional impact of school feeding. The school meal can be shared by children with other household members or can substitute (at least partly) for food normally consumed in the home. This is obvious in the case of take-home-rations, whereby children take home a quantity of food on a regular basis, but also applies to any school feeding programme, because households may in principle use the school meal as a substitute for food normally consumed and spend the monetary equivalent otherwise. Evaluations of fortified biscuit programmes in Bangladesh and Indonesia found that gains in nutritional intake were not limited to the children actually receiving the biscuits at school. The two studies found significant evidence that school children shared the biscuits with their younger sisters or brothers at home. A recent randomised control trial (RCT) in Burkina Faso also found that take-home-ration programmes led to an improvement of the nutritional status of younger siblings in beneficiary households [19]. In Uganda, an RCT also found significant improvements for pre-schooler siblings of children receiving school feeding [20]. This provides emerging evidence of a spill-over effect and a window of opportunity to also affect children during a critical developmental stage when nutritional interventions can have the strongest impact.

Ingested foods contribute to three outcomes, of which physical growth is only one:

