Given the panel structure of the data there is a potential risk of differential attrition. However, it is difficult to predict why households or farmers from the control groups should respond to the interviews in different ways. Refusal to take part in the interview by households not benefiting from the project seems to be the main threat. However, as shown in the table above, the project has limited impact on household expectations in both project and control groups and, therefore, should have limited impact on response rates.

One issue with impact on cognitive development is that the observed impact can be the result of:

•Increased attention in school resulting from the energy meal (short term effect)

•Increased overall cognitive abilities resulting from protracted school feeding, school attendance, play time, social interactions …and so on… (long term effect)

A recent systematic review of school feeding interventions [26] observed that most evaluations have not been able to distinguish the two effects. This could be achieved through careful design of the intervention as the one shown in Table 5. Half of the project children are not given the meal on the day of the test until after the test, while half of the control children are given the meal before the test. The differences across columns (a-c and b-d) should produce the long term effect, while the differences across rows (a-b and c-d) should produce the short term effect. This approach will possibly be tested as a case study in a sub-sample of schools.

**Table 5 T5:** Teasing out short-term and long-term impact on cognitive development

	**Meal**	**No meal**
Project	a	b
Control	c	d

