## Endnotes

^1^ Source: UNESCO Institute of Statistics Mali country profile, 2009.

^2^ Source: Mali Demographic and Health Survey, 2006.

^3^ Ibid, MDHS, 2006.

^4^ Notice that there is a potential nutritional downside on nutrition following from this. If parents believe a child is fed in school when he/she is not, then the child is worse off after the intervention, though possibly just for one or few days.

^5^ Note that in the econometric model we assumed that the schooling choice was made entirely by the parents ignoring the emotional effect of school feeding on children. School fed children may become more motivated and this could lead to higher attendance directly or indirectly (via parents’ decisions). This suggests that the model should include the utility function of children, not just the parents [15].

^6^ We suggest a random selection of households in the villages. This approach has also been successfully adopted, for example, by [22,27]. One additional advantage of this approach is that it allows the identification of the determinants of enrolment/attendance and provide estimates of the relative relevance of school cost reduction effects produced by the programme.

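### Table 5's long-term contrasts (a-c and b-d) are valid only if project and control children have had the same other food before the test, which the protocol's own substitution theory puts in doubt

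*Protocol article*

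**What the plan says.** The Threats to validity section separates a short-term effect (more attention because of the meal) from a long-term one (better cognitive ability after sustained feeding and schooling). Table 5 has four cells: project with meal (a), project without (b), control with meal (c), control without (d).

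- Cell b: "Half of the project children are not given the meal on the day of the test until after the test".
- Cell c: "while half of the control children are given the meal before the test".
- Long-term contrasts: "The differences across columns (a-c and b-d) should produce the long term effect".
- Short-term contrasts: "the differences across rows (a-b and c-d) should produce the short term effect".

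The section adds that this may be tried as a case study in a sub-sample of schools. It gives no sample size, test time or estimator, and does not say whether parents would be told.

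Other sections bear on the rule:

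- Impact on food security and smallholder agriculture: "Substitution occurs when households reduce the domestic consumption of food because children are fed in school".
- Impact on nutrition: the school meal "can substitute (at least partly) for food normally consumed in the home", and this is said to apply to any school feeding programme.
- Endnote 4: "If parents believe a child is fed in school when he/she is not, then the child is worse off after the intervention", possibly for one or a few days. The Risks section repeats this more cautiously.
- The national school feeding programme in Mali: lunch is served at noon, and "school is from 8 am to 12 am and then again from 3 pm to 5 pm", so a control child could eat at home in the break.

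**The concern.** Reading both a-c and b-d as the long-term effect assumes that, within a meal column, project and control children differ only in their longer-term exposure. Their acute state at the test would have to be the same apart from the meal that the design gives or holds back.

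The protocol's own theory gives a reason to doubt this. A project child's household may already have reduced home food in the expectation of a school lunch. A control child's household has no such reason. When the school meal is held back, the project child in cell b may therefore have eaten less than the control child in cell d. The lower test score that results would be counted against the long-term effect.

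The stake is the purpose of the sub-study. The section proposes it because most earlier evaluations could not tell the two effects apart. A rule that can shift part of the lasting effect into the same-day effect weakens that separation.

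**Working it through.** The document gives no figure for this sub-study, so there is none to reproduce. The check is a model of the four cells.

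**Notation.** L is the long-term effect. f(x) is the acute effect of eating x school meals more than a control child's usual intake, with f(0) = 0. B = f(1) is the acute effect of one full meal. q is the share of the meal that project households cut at home.

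**Cells, if the control child's test-day meal is added to an uncut home diet:**

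- a = L + f(1 - q)
- b = L + f(-q)
- c = f(1)
- d = f(0) = 0

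**Contrasts:**

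- b-d = L + f(-q), which is below L for any q > 0.
- a-c = L - [f(1) - f(1 - q)], also below L for any q > 0. With a linear or diminishing response, f(1) - f(1 - q) is no larger than f(0) - f(-q), so a-c loses no more than b-d.
- a-d = (a-b) + (b-d) is an identity, so what b-d loses from L reappears in a-b. The acute part of the total is (a-d) - L = f(1 - q), and a-b exceeds it by -f(-q).

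**Linear case, f(x) = Bx.** a-c = b-d = L - qB, a-b = c-d = B, and the acute part of a-d is (1 - q)B. The two pairs agree with each other, so comparing them would not reveal the bias.

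**If the control child's test-day meal replaces home food instead.** Then c = f(1 - q) and a-c = L, which is unbiased, while b-d is still L + f(-q). Which version applies cannot be known without same-day intake.

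**Illustration.** L = 0.30 SD is borrowed for scale from the expected math effect in Appendix 1. B = 0.10 and 0.20 SD are assumptions. The diminishing curve is f(x) = B(1 - e^(-x))/(1 - e^(-1)). Test-day meal added to the home diet:

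| Response | B | q | a-c | b-d | a-b | c-d | Acute part of a-d |
|---|---|---|---|---|---|---|---|
| either | 0.10 | 0 | 0.300 | 0.300 | 0.100 | 0.100 | 0.100 |
| linear | 0.10 | 0.25 | 0.275 | 0.275 | 0.100 | 0.100 | 0.075 |
| linear | 0.10 | 0.5 | 0.250 | 0.250 | 0.100 | 0.100 | 0.050 |
| diminishing | 0.10 | 0.25 | 0.283 | 0.255 | 0.128 | 0.100 | 0.083 |
| diminishing | 0.10 | 0.5 | 0.262 | 0.197 | 0.165 | 0.100 | 0.062 |
| linear | 0.20 | 0.5 | 0.200 | 0.200 | 0.200 | 0.200 | 0.100 |
| diminishing | 0.20 | 0.5 | 0.224 | 0.095 | 0.330 | 0.200 | 0.124 |

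One worked row (diminishing, B = 0.10, q = 0.5): f(0.5) = 0.10 × 0.3935/0.6321 = 0.062 and f(-0.5) = -0.10 × 0.6487/0.6321 = -0.103. So b-d = 0.300 - 0.103 = 0.197 and a-b = 0.062 + 0.103 = 0.165.

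**Range of q.** The section on food security treats the ration as cash in what it calls a theoretical case: an income elasticity of 0.6 to 0.8 times a food share of 0.8 gives 0.48 to 0.64 spent on food, leaving 0.36 to 0.52 substituted. It presents this as the likely largest substitution and expects the truth to lie between it and none. It is also a household spending share, not one child's intake on one day. About half is therefore a loose upper guide, and zero is the lower end.

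**The case against.** The strongest objection is that little is fixed. The design is an illustration that may be tried in some schools, with details still to be set, and the final analysis plan is to be approved later. That stands and limits the importance of the point. The identification rule itself is nevertheless stated, and it conflicts with the article's own theory.

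Four stronger readings are tempting, and the document does not support them:

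- **Cell b is the child of endnote 4.** Endnote 4 and the Risks section concern food that is not served. In Table 5 the meal is delayed until after the test. The parallel is in the parents' expectation, not in a lost meal. If parents are warned and compensate, the difference disappears.
- **The bias is certain.** The test time is not given. If testing comes before either group would have eaten at midday, a home lunch plays no part, and only cuts at earlier meals would matter.
- **The plan averages a-c and b-d.** It lists both differences and never says to pool them.
- **a-b overstates the short-term effect as the section defines it.** That effect is the attention gained from the meal. With a linear response a-b equals B, which is exactly that. The excess arises only against the acute share of a-d or, with diminishing returns, also against c-d.

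It may also seem enough to drop b-d and keep a-c. That repairs the rule only if the control child's test-day meal replaces home food. If it is added, a-c is biased down as well.

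**Conclusion.** The point holds in a conditional form. Table 5's rule needs two unstated assumptions: no home substitution before the test, and no interaction between programme group and test-day meal. The protocol's own account of substitution casts doubt on the first. To the extent substitution occurs, b-d understates the long-term effect and a-b takes up the difference when a-d is split. The contrast a-c is also too low if the control child's meal is added to an uncut diet, but by no more than b-d under a linear or diminishing response.

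The direction follows from the document. The size does not: it depends on q, on the value of a meal and on the shape of the response, and it is zero if q = 0 or if warned parents compensate. Over q from 0 to 0.5 with L = 0.30, b-d runs from 0.300 down to 0.250 (linear) or 0.197 (diminishing) for B = 0.10, and down to 0.200 or 0.095 for B = 0.20. A reader might infer that the design would hide the lasting effect or show harm. That takes larger assumed meal effects or more substitution than the document expects.

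This is a minor point. It concerns an optional case study and touches no primary comparison.

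**What to change.** If the case study goes ahead, amend the Table 5 text in Threats to validity as follows:

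1. State that the rule assumes no home substitution before the test and no interaction between programme group and test-day meal.
2. Do not label b-d, or a-c, as the pure long-term effect.
3. Report all four contrasts with the interaction, and a-d as the total effect.
4. Record what each tested child ate that day before the test, and use it to check or adjust the contrasts. This is the essential item, because with a linear response the two pairs can agree while both long-term contrasts are biased.
5. Test all four cells at the same clock time.

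The cost is one extra question on the test form, some scheduling, and a less clean separation of the two effects than the present wording promises.

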### Survey instruments

The impact evaluation will include household, school, farmer, village and commune level data collection.

Household questionnaire: This will collect data at the household level and for each household member separately.

The household questionnaire will include the following modules:

◦ Household roster (main demographic characteristics, including those of children residing elsewhere)

◦ Education (school attendance, education of all household members, time spent in class and working, distance and transport to school, meals while in school, parents’ aspirations, PTA membership and involvement)

◦ Household assets and farm assets (household facilities and durables, including land and livestock holdings)

◦ Economic activities (simple income questionnaire on time spent working by household members in wage work, own business and own farm)

◦ Expenditure (monetary expenditure and own production of food, education, health, durables and non-food expenditure)

◦ Anthropometry (height and weight of parents and children above six months of age – parents’ measurements are taken to assess the genetic potential)

◦ Cognitive and achievement tests (test scores on math, language and digit span test),

◦ Farm income (agricultural production and revenues, input expenditure and depreciation of farm assets)

◦ Other income (a simplified income questionnaire for other income sources like microenterprises, transfers, remittances, gifts and so on)

School questionnaire: In each school a questionnaire will be administered to head teachers and teachers, and will include the following modules:

◦ School facilities (school characteristics including boards, toilets, furniture, books and all school-feeding related characteristics – kitchen, storage room and so on)

◦ School participation (school-level data on enrolment, attendance and drop-out)

◦ School management and food procurement

◦ Teachers (qualifications, living conditions and aspirations)

◦ Training and monitoring activities

Mayors’ questionnaires: Mayors will be interviewed in each of the 58 communes at the baseline and at the endline. The purpose of the questionnaire is two-fold. First, it will collect information at the village level that will be used in the multivariate analysis when analysing the project outcomes at the household level. Second, some project outcomes, for example, the number of small farmers involved in the project, will be observed through this instrument. The tool will include the following modules:

◦ Funding of school canteens (instalments received and payments made)

◦ Food deliveries (quantities and characteristics of delivery to each school)

◦ Food procurement (details of all procurement over the calendar year)

◦ Monitoring and supervision (supervision of correct procurement and deliveries)

◦ Knowledge and practices (training and knowledge acquired)

An operations manual, including guidelines for the survey data collection was developed as part of the baseline survey training materials. The manual included background information on the survey activities, module by module guidance on the different survey tools, as well as specific guidance on the anthropometry measurements.

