### The HGSF pilot

An innovative capacity-building component will be integrated alongside the national school feeding programme and will constitute one of the treatment arms of the experiment (see Figure 2). The HGSF pilot intends to promote purchases from small farmers through training, monitoring and communication activities among the actors involved. Mayors and CAPs will be instructed, and encouraged, to involve small farmers in the transactions. Currently, mayors purchase food from one or more traders following government guidelines regarding contracts and bidding processes. Under the project, and in coordination with the Ministry of Agriculture, mayors and traders will be requested to enforce the purchase of food from local producers at least at a minimum percentage. On the other hand, the CGSs will be assigned the task of identifying local suppliers, possibly at the village level, and of establishing contacts between these suppliers and the traders.

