**Figure 2 F2:**
[figure not shown]
Stylised food procurement process in the HGSF+ programme.

A working group composed of in-country stakeholders, including the Dutch Cooperation Agency (SNV), Catholic Relief Services (CRS), and WFP is currently working on the details of the package of “software” interventions to improve overall programme performance. This package will include:

•Training of mayors and CAPS. At the beginning of each school year a number of training events will be organised for Commune-level stakeholders, including mayors and CAP. The purpose of the training events is to improve service delivery on several accounts:

◦ The establishment of a monitoring system of programme activities

◦ The identification of formulas for the allocation of food to schools (currently the allocation is based on rough enrolment estimates, but enrolment is endogenous as it is driven by food provision, hence a flexible system of funds and food allocation based on ‘predicted’ enrolment needs to be put in place.)

◦ The illustration of methodologies for purchasing from smallholder farmers rather than from traders (formulation of bids, contracts, contingency plans and so on)

◦ Nutrition education and the importance of adequate nutrition for school children and smallholder farmers, for example, how to use the foods they grow or purchase to improve the nutritional status of all family members, including diet diversification, availability of staple and nutrient rich foods by season, food storage and safety, food processing and preparation.

•Training of CGS. Training events for CGS at the village level will be held periodically, on a monthly or quarterly basis, in every intervention village:

◦ Members of CGS will be given the instruments to efficiently implement the programme including basic accountancy skills, information on their rights and entitlements, and information on methods to raise complaints

◦ Participatory monitoring events will be periodically held at the village level. +Members of CGS, parent teacher associations (PTAs), and parents will be involved in participatory events where the programme performance will be monitored in close detail, suggestions for improvement will be proposed and complaints brought to the attention of project staff and CAPs.

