**Figure 4 F4:**
[figure not shown]
Programme theory of school feeding and smallholder agriculture.

**Table 1 T1:** Programme impact on smallholder farmers

** Effects**	**Impact on smallholder farmers**	** Spill-over effects**
Output effects	Increase in farm profits	Increase in consumer prices
Distributional effects	Increase in farm profits	Decrease in large farmers’ profits
Stabilisation effects	Risk reduction	none

The programme introduces additional demand on the market. In Mali, the school feeding programme purchases food for schools at the Commune level, which includes several villages. Most Communes have food markets. Mayors purchase from traders in the commune. Traders in turn purchase food from, among other sources, small-holder farmers. The effect of the food purchases is a shift of the demand curve for food (say rice) to the right (movement from D_0_ to D_1_), as illustrated in Figure 5.

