### Main hypotheses and outcome indicators

We summarise here the expected impact of the intervention on education, nutrition and social protection discussed in Section Programme theory of the intervention.

•The intervention will have an impact on a small number of farmers in the intervention villages. Other persons in the village may benefit either directly or indirectly via an increase in income.

•The intervention will have a positive impact on enrolment, attendance and drop-out rates.

•The intervention will have an impact on cognitive abilities and class behaviour, including attention.

•The impact on learning (test scores) will be moderate as school quality is unlikely to change in the short term.

•The intervention will have a limited impact on physical growth of children because of the increase in PAL, substitution effects and the age range (6 to 17 years) of the targeted population. An impact on siblings of school-going children is possible if substitution effects are strong.

•The intervention will have a moderate impact on the diet because food purchases by communities and mayors do not follow nutritional guidelines and nutrition education is absent.

•The intervention will have little or no impact on micronutrient status as the food provision is not fortified and only moderate effects on diet diversity are expected.

•The overall impact of the programme will increase through the introduction of social accountability mechanisms and the strengthening of the monitoring and communication system.

Table 2 includes a list of the main outcome indicators of the study. Section Methods of analysis will describe how data will be collected using different survey instruments. All outcomes, including school attendance and test scores, will be obtained at the household level.

**Table 2 T2:** Main outcome indicators of the intervention

** Indicator**	** Metric**
Income	Farm profits
Distributional effects	Small farmers participating in the programme
Schooling	Enrolment, attendance, and completion
Attention	Digit span or other test
Learning achievements	Scores on language and math tests
Physical growth	Anthropometric measures of height and weight
Diet diversity	Household consumption
Social accountability	Parental monitoring and motivation

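### The count of small farmers supplying the programme comes from mayors, whose knowledge and incentive to report may differ between the feeding arms, and the article contradicts itself on this data source

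*Protocol article*

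**What the plan says.** Table 2 of the protocol article gives "Small farmers participating in the programme" as the metric for distributional effects. Two sections then disagree on where it comes from:

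- Main hypotheses and outcome indicators: "All outcomes, including school attendance and test scores, will be obtained at the household level".
- Survey instruments, on the mayors' questionnaire: "some project outcomes, for example, the number of small farmers involved in the project, will be observed through this instrument". The same paragraph adds: "Mayors will be interviewed in each of the 58 communes at the baseline and at the endline".

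On the supply chain, the description of the national programme says: "The service providers (traders) then purchase the food from the market or from small-holders, and deliver it to the relevant schools". The section on smallholder agriculture repeats it: "Mayors purchase from traders in the commune. Traders in turn purchase food from, among other sources, small-holder farmers".

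On what HGSF+ adds, the section on the pilot says that "mayors and traders will be requested to enforce the purchase of food from local producers at least at a minimum percentage", and that mayors are to be instructed and encouraged to bring small farmers into the transactions. The training package for mayors includes "The establishment of a monitoring system of programme activities" and methods for buying from smallholders.

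**The concern.** This indicator is the most direct evidence on whether HGSF+ moves purchases towards small farmers. Its reporter is the mayor, and the mayor is also a target of the HGSF+ package. Two things about that reporter may change with the arm:

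- **Knowledge.** A mayor who contracts a trader need not know which farms the food came from. Training, record-keeping and direct-purchase methods may make suppliers more visible in HGSF+.
- **Incentive.** An HGSF+ mayor reports against a local share that he or she was asked to enforce. A mayor in the regular arm does not.

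Both point the same way. Part of any HGSF+ advantage on this count could therefore come from fuller reporting and not from more farmers supplying. Separately, the article must say which of its two statements on the data source holds.

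**Working it through.** **1. Unit of report.** HGSF+ and regular feeding are compared by commune, 29 versus 29 (Table 3), and 58 mayors are interviewed. That is one mayor's report per randomised unit. Each commune also contains a control school, which receives no programme food, so the count bears only on HGSF+ versus regular feeding.

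**2. The reporter in the two arms.**

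| | Regular feeding | HGSF+ |
|---|---|---|
| Route of purchase | Mayor to trader; trader chooses the source | Traders remain in the chain; mayors are also taught to buy from smallholders |
| Instruction to involve small farmers | Not stated | Yes |
| Minimum local share requested | Not stated | Yes, level not given |
| Training of mayors | Not part of the arm | Each school year |
| Monitoring system in the package | Not part of the arm | Yes |

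The outcome section also treats what mayors know and do as something that training should change, and the mayors' questionnaire has a module for it. So the reporter's knowledge is an intended effect of treatment.

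**3. Do the planned safeguards remove it?**

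- Randomisation and restricted randomisation balance communes. They do not act on how the outcome is measured afterwards.
- Difference-in-difference removes reporting differences that are constant over time. Here the change comes after baseline and in one arm only.
- The section on threats to validity says each outcome indicator was examined, but Table 4 has no row for small-farmer participation.

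**4. Size.** The article gives no rate, sample size or power for this count, so there is no figure to reproduce. What follows is illustration, and every input is an assumption. Let both arms truly have a mean of m suppliers per commune, with mayors reporting a share s0 (regular) or s1 (HGSF+). The reported means are m × s0 and m × s1, so the spurious ratio is s1/s0.

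Simulation: 29 versus 29 communes; m = 3, 5 or 10; counts Poisson with gamma variation between communes (coefficient of variation 0.5); t-test at two-sided 0.05; 3,000 trials per cell; no true difference.

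| s0 | s1 | Ratio s1/s0 | Significant, m = 3 | m = 5 | m = 10 |
|---|---|---|---|---|---|
| 0.8 | 0.8 | 1.00 | 5.6% | 5.0% | 4.7% |
| 0.7 | 0.8 | 1.14 | 9.1% | 10.1% | 13.8% |
| 0.6 | 0.8 | 1.33 | 24.0% | 28.8% | 40.1% |
| 0.5 | 0.8 | 1.60 | 50.3% | 63.5% | 78.2% |
| 0.4 | 0.8 | 2.00 | 80.1% | 91.5% | 96.9% |

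A 10-point gap in reporting does modest harm. A gap of 20 points or more makes the test unreliable. The direction follows from setting s1 above s0.

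**The case against.** The case on the other side has real force.

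- **Knowledge is inferred.** No sentence says that mayors cannot see past the trader. The article also says that communes or school committees procure from local markets. The mayors' tool asks for payments, deliveries to each school and a year's procurement in detail, so it rests partly on transactions. This stands, and it is why the point is a risk and not a demonstrated bias.
- **Supplier lists.** A reader might infer that HGSF+ mayors are handed the names of local suppliers. The pilot section says that school committees identify suppliers and link them to the traders. The argument cannot rest on that.
- **Monitoring.** Monitoring visits are also described for the programme generally, so the difference in records may be smaller than the package suggests.
- **Weight of the indicator.** A reader might infer that, with income underpowered for HGSF+, the plan will lean on this count. The appendix names restricted randomisation and farm inputs and capital as its remedies, and elsewhere the article adds simulations. The abstract's list of primary outcomes does not name the count.
- **Other sources.** The school procurement module, farmers' revenue data and expenditure tracking exist. None is tied to this count, but they make checking easy.

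How the count is built may be set out in the questionnaire or operations manual, which are not shown. That does not resolve the contradiction on the source, nor the explicit choice of the mayor as reporter.

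**Conclusion.** The point holds as a risk of differential ascertainment in one indicator and one contrast: small-farmer participation, HGSF+ versus regular feeding. The mayor as source, purchase through traders and the HGSF+ instructions to mayors are all stated. That reporting differs by arm, and favours HGSF+, is a reasonable inference from information and incentive together. It is not established.

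The size cannot be derived from the documents. The tables above show sensitivity to assumed reporting rates and do not estimate the bias. A reader might go further and conclude that the instrument is bound to show more small farmers under HGSF+, or that the trial's main results are compromised. The documents support neither: farm profits, enrolment and test scores do not come from mayors and are unaffected.

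The contradiction between the two sections on the data source stands whatever the size of the bias.

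**What to change.** 1. At endline, ask every sampled farmer household in the intervention villages, in identical words in both feeding arms, whether and how much it sold in the past year, by type of buyer: school, school committee, commune or trader.
2. Make the proportion selling and the quantity sold the main measure for HGSF+ versus regular feeding, analysed by commune. Report direct sales and total quantity sold separately from sales that the farmer attributes to school meals.
3. Keep the mayors' count as a process measure, checked against the school procurement module and the expenditure tracking.
4. Add the outcome to Table 4, and reconcile the outcome section with the survey-instruments section on its source.

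**Cost.** A few questions in the farm-income module already planned for 290 farmers per feeding arm (29 villages × 10).

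**Limits.** The sample is up to 10 nominated surplus farmers per project village, so it does not give the commune total. Some farmers will not know a trader's end buyer, possibly less often in HGSF+, which is why step 2 separates the kinds of sale.

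Precision is also modest. If the article's income intra-class correlation of 0.25 applied (an assumption), the design effect would be 1 + 9 × 0.25 = 3.25 and the effective sample 290/3.25 = 89 per arm. The detectable difference at 80% power would be 2.80 × √(2/89) = 0.42 standard deviations, close to the 40% stated for income. For a proportion near one half that is about 0.42 × 0.5 = 21 percentage points. The gain is a comparison that does not rest on the mayor, not a more powerful one.
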